### Data collection

Participants will be included in the study and will undergo several follow-up visits. During the follow-up period trained research nurses/data managers will contact patients at baseline (T=0) (± one week), and subsequently every four weeks (± two weeks), to go through a standardized questionnaire and to collect data on the outcomes of sequelae and clinical symptoms/AEs. In addition, all patients will be contacted by the research nurse/data manager at the end of the APA period (± two weeks from the end) to complete a last questionnaire. Research nurses/data managers additionally will collect required laboratory and or test results from participants’ (electronic) medical records. If a subject discontinues the APA and lifestyle interventions during the 12-week follow-up period, follow-up will continue.

The questions within the surveys will be performed to assess the occurrence and severity of any new symptoms experienced by the participants, and the global physical and psychological health after the beginning of APA. The questionnaires that will be administered to participants during the study period are listed in **Table 4**.

**Table 4 T4:** Type of questionnaire that will be administered to breast cancer patients.

Objective	Questionnaire
**Disability**	The DASH (disabilities of the arm, shoulder, and hand measurement tool) questionnaire
**QoL**	EORTC qlq-C30 and EORTC qlq- BR23 questionnaire
**Fatigue**	The MFI 20 (Multidimensional fatigue inventory) questionnaire
**Anxiety-depression**	The HADS (Hospital anxiety and depression scale) questionnaire
**Physical activity and sedentary behavior**	The short version of the IPAQ (international physical activity questionnaire)
**Oedema assessment**	Disability scale for oedema

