### Design of FENICE trial

The FENICE study is a mono-center, randomized clinical trial targeting women with stages I-III BC within four weeks from surgery, conducted at the Breast Unit of Policlinico Tor Vergata Rome and Frascati Scherma ASD. The sequence of study and control group is randomized to minimize the influence of time-dependent variables. The participants, regardless of arm dominance, will be followed up by oncologists, radiotherapists, and surgeons according to the BC guidelines. All subjects participating in the study will undergo a sports medicine examination to objectify whether there are any alterations or diseases that pose a risk to the patient and to determine whether the patient needs to have additional tests and more specific examinations performed. For participants in the study arm only, APA consists of two fencing sessions (1 h/session) per week within 15 days of enrollment. The minimum number of sessions for the assessment of the primary endpoint is 48 sessions over six months up to a maximum of 96 sessions over 12 months (**Figure 2**).

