### Follow up visits

Participants will be included in the FENICE study for a total of 24 months and will be followed up differently based on the inclusion arm. In the study arm (APA and Mediterranean diet arm) patients will be monthly followed up for comorbidities, co-medication and herbal remedies, adverse events, and body mass index (BMI). Moreover, every three months also clinical evaluation, blood parameters, instrumental exams and QoL questionnaires will be carried out for the study arm patients. In the control arm, instead, all the mentioned parameters will be followed up every three months (see **Figure 2**).

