### Sample size

The hypothesis guiding the formal determination of the sample size proposes an expected improvement of at least 15 points in the mean DASH score. The DASH score is a valuable, pragmatic, and frequently utilized metric in individuals with various musculoskeletal disorders of the upper limb. Ranging from 0 to 100, it encompasses responses to 30 questions (https://orthotoolkit.com/dash/) An improvement of at least 15 points is considered clinically significant in enhancing functional ability. The statistical parameters are configured in a highly conservative manner, considering the non-pharmacological nature of the intervention (adapted physical activity) and the inherent inter-individual variability in response, particularly within the treated group (Group 1). Therefore, with alpha and beta errors set at 0.01, a standard deviation in Group 1 that is twice that of Group 2 (SD: 20 compared to 10), even exceeding the hypothesized difference (15 points), 56 patients per group are deemed necessary. Considering the enrollment capabilities of our group and potential physiological withdrawal of patients, the sample size has been increased to 150 total patients. The target population will be at least 18 years of age (of any ethnicity) with a diagnosis of non-metastatic breast cancer and already treated with surgery for the primary tumor. This total will be divided into two sub-groups by randomization in blocks of 75 patients each (intervention group, Group 1, and control group, Group 2). The first group will be distinguished by subjects treated with adapted physical activity rehabilitation and with correct lifestyle suggestions. The second group, on the other hand, will be characterized by standard care without physical activity rehabilitation or lifestyle suggestions.

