## Discussion

Regular physical activity performed during and after a BC treatment has been shown to improve quality of life (QoL) (34, 35). However, the type of exercise and the time spent on it are still based on patient’s will. Recently, a rehabilitation program was launched in France for women treated for BC that used adapted fencing as a rehabilitative activity. The RIPOSTE program aimed to offer adapted fencing to patients with BC (30, 43). In Italy, several authorities, including scientific associations (LILT – Lega Italiana per la Lotta ai Tumori), sports federations and Institutions (FIS – Federazione Italiana Scherma, CONI – Comitato Olimpico Nazionale Italiano) are committed to raising awareness of cancer patients and physicians on APA, diet, and correct lifestyle, throughout the promotion of observational studies, sporting, and popular events (“Nastro rosa”, “rema Roma per la vita”). With the FENICE study protocol, the initiative is intended to introduce the discipline of fencing into the rehabilitation program for women who have undergone surgery for breast cancer. Usually, after surgery, there is excessive internal rotation of the shoulder, which affects the patient’s posture, and fencing, especially the guard position, promotes an improvement of this condition. In addition, the range of motion resulting from increasingly higher parries under the guidance of the fencing master promotes the mobility of the arm and shoulder, which are limited by surgical scars and adhesions. The laterality of the exercise and the type of weapons used (foil and saber) allow constant work on mobilizing the operated shoulder and arm, especially since it is an upper-body activity that focuses on the upper body, from the belt to the head. (30, 43). Finally, the strong concentration and determination that fencing requires will certainly have a positive effect on image, mood, and mental strength, which are very often compromised following breast surgery. We firmly believe that the FENICE study by introducing adapted fencing in the near postoperative period, can be an effective tool to improve the physical and mental health of patients who have undergone surgery for BC. To date, the importance of adapted physical activity as a rehabilitation measure is emphasized in the literature, especially for cancer patients. In Italy, however, APA remains limited to local initiatives without being promoted by the health authorities. In some countries, such as France and the United Kingdom, APA is recognized as a prescription treatment for chronic diseases. As APA is therefore reimbursed by the health system, the sports doctor can prescribe a physical rehabilitation activity such as a medication or an examination. We hope that the FENICE protocol will be a pilot study for large-scale clinical trials that can lay the foundations for nationwide recognition of APA in the Italian healthcare system. Alongside the key role of the sports physician in APA implementation, this initiative might shed light on the role of physical activity and rehabilitation in improving WA of breast cancer patients since data from the literature are to date inconsistent (51). Currently, there is a lack of uniform and shared guidelines that can evaluate the Work Ability Index (WAI) through interventions or rehabilitative activities that support the patient’s return to work or, possibly, retention. Recently, the “Beyond Cancer” program by Sheppard and colleagues tried to overcome these barriers to sustainable return to work for women with breast cancer (52). In that perspective the FENICE study, as a tailored occupational rehabilitation intervention, may also include in its multidisciplinary network occupational physicians to assess the actual benefit of PA in promoting patients’ return to work and employability through dedicated questionnaires for participants in the adapted fencing group.

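### The questionnaires are timed by the start and end of APA, which controls never have, and the text leaves open whether staff lead the patient-reported instruments

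*Protocol article*

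**What the plan says.** All of this is in the protocol article.

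- **Data collection, contacts.** Research nurses or data managers contact patients at baseline and then every four weeks (± two weeks) "to go through a standardized questionnaire and to collect data on the outcomes of sequelae and clinical symptoms/AEs".
- **Data collection, purpose of the surveys.** They are to assess new symptoms and "the global physical and psychological health after the beginning of APA".
- **Data collection, last questionnaire.** "all patients will be contacted by the research nurse/data manager at the end of the APA period" (± two weeks), to complete it.
- **Design of FENICE trial.** "For participants in the study arm only, APA consists of two fencing sessions (1 h/session) per week within 15 days of enrollment". The course runs from 48 sessions over six months to 96 sessions over 12 months.
- **Sample size.** The control group "will be characterized by standard care without physical activity rehabilitation or lifestyle suggestions". The calculation rests on a 15-point difference in mean DASH score.
- **Table 4.** It lists DASH, EORTC QLQ-C30 and BR23, MFI-20, HADS, short IPAQ and an oedema disability scale.
- **Follow up visits.** Some items are monthly and others, including the QoL questionnaires, three-monthly in the study arm. "In the control arm, instead, all the mentioned parameters will be followed up every three months".

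**The concern.** A randomised comparison of questionnaire scores needs both arms to be asked about the same period, at the same time after randomisation and in the same way. Here the period and the final time point are both defined by an event that occurs in one arm only. Someone must choose a substitute date for each control. If the choice differs from the study-arm date, the arms are compared at different times since surgery. Women enter within four weeks of surgery, so any change in arm function over the following months would then appear as a difference between arms.

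The second strand is how answers are obtained. Participants know whether they are fencing, and most outcomes in Table 4 are subjective. If staff took patients through those instruments with APA as the stated reference, answers could shift towards the study arm. A participant's own knowledge of her arm cannot be removed. The time reference and the mode of completion can be made the same in both arms.

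**Working it through.** **Step 1. Set the time references side by side.**

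| Reference used in Data collection | Study arm | Control arm |
|---|---|---|
| Beginning of APA | Tied to enrolment: within 15 days | Does not occur; no substitute given |
| End of APA period (last questionnaire) | Six to 12 months of sessions | Does not occur; no substitute given |

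At two sessions a week, 48 sessions take 48/2 = 24 weeks and 96 take 96/2 = 48 weeks. The last questionnaire therefore has no single time even within the study arm. A control assessed at the short end and a study-arm patient at the long end would be six months apart. The same section also mentions a 12-week follow-up period, which matches neither limit and supplies no alternative clock.

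**Step 2. Does the text say staff lead the Table 4 instruments?** The sentence on going through a questionnaire uses the singular and links it to sequelae, symptoms and AEs at four-weekly contacts. The next paragraph speaks of questions within the surveys, then lists Table 4 as questionnaires administered to participants. The Follow up visits section puts QoL questionnaires on a three-monthly schedule. One reading joins the two activities and another separates them. The mode of completion is not fixed either way.

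**Step 3. Reproduce the plan's sample size, to confirm the SDs used in the illustration.** Inputs from Sample size: difference 15, SD 20 and 10, alpha 0.01, beta 0.01.

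- Normal approximation, two-sided: n = (2.576 + 2.326)² × (20² + 10²) / 15² = 24.03 × 500/225 = 53.4, so 54 per group.
- Noncentral t, two-sided: 56 per group, power 0.990. The stated 56 reproduces.

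**Step 4. Illustration under an assumed shift.** The documents give no size for any reporting bias. Suppose the true effect is zero and study-arm scores are better by b points for any non-causal reason.

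- SE with 75 per arm = √(400/75 + 100/75) = √6.667 = 2.58.
- b/SE for b = 2, 3, 5 is 0.77, 1.16, 1.94.
- Chance of p ≤ 0.05, the threshold in Statistical analysis (two-sided, noncentral t): 12%, 21%, 48%. The normal approximation gives 49% for the last.
- With 56 per arm, if withdrawals used up the whole margin: 10%, 17%, 38%.

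For the timing strand alone, a shift of 2 to 5 points across a six-month gap would need an average change of 2/6 = 0.33 to 5/6 = 0.83 DASH points per month. Its direction would depend on which arm was assessed later.

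**The case against.** The strongest reply is that the text establishes less than a reader might infer.

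- **That staff lead DASH, HADS, MFI-20 and the EORTC forms.** Not stated. What staff go through may be a symptom and AE checklist, which staff ordinarily collect, and patients are contacted to complete the last questionnaire, which fits self-completion. This objection stands, so interviewer bias is only a possibility.
- **That study-arm women are asked how they have been since starting fencing.** No item wording is shown. The phrase about the beginning of APA is the authors' description of purpose and may mean only a time window. Table 4 gives no arm-specific versions. This also stands, but a window that starts with APA is still undefined for controls.
- **That the data collectors expect fencing to work.** The Discussion says that the concentration and determination fencing requires "will certainly have a positive effect on image, mood, and mental strength". That is the authors' view of mood and image. It says nothing about the nurses or data managers, or about arm function, and is not evidence on how answers are collected.
- **That the false-positive rates measure this trial's bias.** They do not. The shift is assumed, and nothing separates staff influence from the participant's own expectation.
- **That a condensed article may leave mode of completion and masking of collectors to the full protocol.** True, and their absence alone would be no finding. The time references are different: the article states them, and they fit one arm only. Contacts anchored to APA would also work against any masking of collectors described elsewhere.

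**Conclusion.** The point holds in a limited form. The documents establish that the surveys' reference point and the last questionnaire's timing depend on APA, that only the study arm has APA, and that the article gives no equivalent for controls. They also establish staff-led contact, in a trial whose participants cannot be masked and whose sample size rests on a questionnaire score.

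They do not establish that staff administer that questionnaire, so interviewer bias remains a possible exposure of unknown size. The figures of 12% to 48% rest on an assumed 2 to 5 point shift, the plan's SDs and 75 analysed per arm. They show only that a shift of up to one third of the 15-point target (5/15) would matter at the 0.05 threshold. The change should be made because it is cheap and removes an avoidable difference between arms, not because a bias of known size has been shown.

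**What to change.** Amend the Data collection section.

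1. Define every questionnaire time in both arms as a fixed interval from randomisation, with the same window. Set one final time for all patients in place of the end of the APA period.
2. Replace the reference to the beginning of APA with time since randomisation or each instrument's own recall period. Use no wording that names APA.
3. State that patients in both arms complete DASH, QLQ-C30/BR23, MFI-20, HADS and IPAQ themselves, before any discussion with staff at that contact. Limit staff to a completeness check on these forms, and state separately which symptom and AE data staff collect.

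The oedema scale is left out of item 3 because the article does not describe how it is completed; the authors should say.

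These are changes of wording and forms and need no added visits. The downside is slightly more missing items, which the completeness check limits.

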### Sample size

The hypothesis guiding the formal determination of the sample size proposes an expected improvement of at least 15 points in the mean DASH score. The DASH score is a valuable, pragmatic, and frequently utilized metric in individuals with various musculoskeletal disorders of the upper limb. Ranging from 0 to 100, it encompasses responses to 30 questions (https://orthotoolkit.com/dash/) An improvement of at least 15 points is considered clinically significant in enhancing functional ability. The statistical parameters are configured in a highly conservative manner, considering the non-pharmacological nature of the intervention (adapted physical activity) and the inherent inter-individual variability in response, particularly within the treated group (Group 1). Therefore, with alpha and beta errors set at 0.01, a standard deviation in Group 1 that is twice that of Group 2 (SD: 20 compared to 10), even exceeding the hypothesized difference (15 points), 56 patients per group are deemed necessary. Considering the enrollment capabilities of our group and potential physiological withdrawal of patients, the sample size has been increased to 150 total patients. The target population will be at least 18 years of age (of any ethnicity) with a diagnosis of non-metastatic breast cancer and already treated with surgery for the primary tumor. This total will be divided into two sub-groups by randomization in blocks of 75 patients each (intervention group, Group 1, and control group, Group 2). The first group will be distinguished by subjects treated with adapted physical activity rehabilitation and with correct lifestyle suggestions. The second group, on the other hand, will be characterized by standard care without physical activity rehabilitation or lifestyle suggestions.

### Statistical analysis

The descriptive statistical analyses, the central tendency, variability, symmetry and kurtosis will be calculated, all accompanied by appropriate graphical representations. Regarding the inferential analyses, we will continue with the verification of the parametric and non-parametric hypotheses, respectively for the quantitative variables with parametric tests such as: Student’s t-test, Fisher’s F-test, etc. and for categorical variables using non-parametric tests such as: chi-square, Mann Wittney’s U, Fisher’s exact test, etc. Only results with p-values ≤ 0.05 will be considered statistically significant. Principal component analysis (PCA) will be adopted to explore the relationships among secondary variables and identify patterns of improvement related to the APA intervention (50).

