Adapted fencing includes offensive and defensive actions, which are performed considering the mobility of the shoulder. The primary (tierce = outside; quart = inside; fifth = head) and secondary blocks are therefore performed by patients with maximum mobility, without ever causing pain. Coordination, agility, and strength are encouraged during exercises between patients and during lessons with the fencing master. The adapted fencing lesson ends with a cool-down period. Since different subjects experience different physical outcomes for the cancer and the subsequent treatment, the program must address these individual needs while respecting safety principles. Therefore, rest and water breaks will be provided when necessary, and simplified or less strenuous movements will be suggested as alternatives for those who find parts of the workout too challenging or unsafe. In addition, participants are encouraged to use both saber and foil, also depending on which master is holding the training session. In any case, the weapons used will be adapted in material to avoid excessive strain or fatigue as stated above. Moreover, the courses and masters allow 12 participants per session with a maximum ratio of 1 master per 2.5 participants. During the study protocol, participants are also encouraged to follow healthy diet and adhere to the standards of the Mediterranean diet through the prescription of a personalized diet by a nutritional biologist involved in the project. Conventional bioelectrical impedance (BIA) testing to assess body composition is also planned during protocol follow-ups. To assess adherence to the Mediterranean diet, the Prevención con Dieta Mediterránea (PREDIMED) questionnaire will be completed both at the beginning and at the end of the study (49). The participants of the FENICE study will be followed up by several specialists before and during the APA period (**Figure 3**). This study was approved by the ethic board of the Policlinico Tor Vergata of Univeristy of Rome and the enrollment will start in September 2024 and the recruitment will take an 18 months’ time window for the inclusion of the expected 150 participants.

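### Fencing is delivered in shared courses in the study arm only, but the sizing and the tests named for quantitative outcomes assume that women are independent; if outcomes within a course are positively correlated, the false-positive rate exceeds the nominal 5%

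*Protocol article*

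**What the plan says.** **Delivery.** The Design of FENICE trial section gives fencing to the study arm only, in two one-hour sessions a week, for 48 sessions over six months up to 96 over twelve. On grouping it says: "the courses and masters allow 12 participants per session with a maximum ratio of 1 master per 2.5 participants". On contact between participants: "Coordination, agility, and strength are encouraged during exercises between patients and during lessons with the fencing master". The choice of weapon depends partly on which master leads the session. Controls receive standard care with no training sessions.

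**Sizing.** The Sample size section "proposes an expected improvement of at least 15 points in the mean DASH score", "with alpha and beta errors set at 0.01", and takes "a standard deviation in Group 1 that is twice that of Group 2 (SD: 20 compared to 10"). The result is that "56 patients per group are deemed necessary". The total is then raised to 150 (75 per arm), for recruitment capacity and expected withdrawals.

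**Analysis.** The Statistical analysis section plans to proceed "respectively for the quantitative variables with parametric tests such as: Student’s t-test, Fisher’s F-test, etc", with significance at p ≤ 0.05. The article mentions no ICC, design effect, or course or master term.

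**The concern.** Women are randomised individually, but one arm is then treated in groups and the other is not. This is a partially nested design. Shared teaching and partner exercises over 6 to 12 months can make the outcomes of women in the same course more alike. The study-arm mean then varies more than the independent-sample formula allows.

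At stake is the error rate for the DASH comparison and for every other quantitative outcome that training can affect. A chance difference between a few courses and the controls could be declared an effect of the programme. Changing to an unequal-variance t-test does not help, because the problem is correlation within courses. At ICC 0.05 with six courses of 12, that test has a 10.3% false-positive rate, against 10.4% for Student's t.

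**Working it through.** **Inputs from the article:** difference 15; SD 20 (study) and 10 (control); alpha = beta = 0.01 for sizing; p ≤ 0.05 for analysis; 75 per arm; 12 per session; at most 2.5 women per master.

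**Assumed, because the article does not give them:** ICC from 0.01 to 0.10, and the effective cluster size m.

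**Step 1: reproduce the plan's figure.** With independent women and a two-sided test,

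n = (20² + 10²)(2.576 + 2.326)² / 15² = 53.4, so 54 per group.

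The noncentral-t version gives exactly 56. The sizing is therefore an independence calculation.

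**Step 2: inflation of the standard error.** The design effect applies to the study arm only:

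DE = 1 + (m − 1) × ICC

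SE ratio = √[(400 × DE + 100) / 500]

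True two-sided error at nominal 0.05 = 2 × [1 − Φ(1.96 / SE ratio)]

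For m = 12 and ICC 0.05: DE = 1.55; variance ratio = (620 + 100)/500 = 1.44; SE ratio = 1.20; error = 2 × [1 − Φ(1.633)] = 10.2%.

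| m = 12, SD 20/10 | DE | SE ratio | False-positive rate |
|---|---|---|---|
| ICC 0.01 | 1.11 | 1.04 | 6.0% |
| ICC 0.02 | 1.22 | 1.08 | 7.1% |
| ICC 0.05 | 1.55 | 1.20 | 10.2% |
| ICC 0.10 | 2.10 | 1.37 | 15.3% |

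Simulating Student's t with 75 per arm and 6 or 7 courses gives 10.4-10.5% at ICC 0.05 and 15.4-15.9% at ICC 0.10.

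**Step 3: vary what the article leaves open, at ICC 0.05.**

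| Structure | DE | Variance ratio | False-positive rate |
|---|---|---|---|
| Equal SDs, m = 12 | 1.55 | (1.55 + 1)/2 = 1.275 | about 8% |
| m = 2.5 (women per master), SD 20/10 | 1.075 | (430 + 100)/500 = 1.06 | about 6% |
| m = 5, SD 20/10 | 1.20 | (480 + 100)/500 = 1.16 | about 7% |
| Rolling entry, 4 slots (m ≈ 19), SD 20/10 | about 1.89 | about 1.71 | about 14% |
| Rolling entry, 3 slots (m = 25), SD 20/10 | 2.20 | (880 + 100)/500 = 1.96 | about 16% |

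**Step 4: power at 75 per arm, ICC 0.05, m = 12.** SE = √[(400 × 1.55 + 100)/75] = 3.10. By the normal approximation, power at alpha 0.01 is Φ(15/3.10 − 2.576), about 98.8%. This ignores that 7 courses leave few degrees of freedom. Comparing course means with individual controls, with Satterthwaite degrees of freedom, gives by simulation about 89% at alpha 0.01 and 99% at alpha 0.05. With 6 or 7 courses that test keeps the false-positive rate near 5-6%. With only 3 or 4 slots its error is 6-8%, and its power at alpha 0.05 is 71-88%.

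**The case against.** **The list of tests is open, and an unseen analysis plan may deal with clustering.** This stands in part. Student's t is given as an example and is not assigned to DASH, so it cannot be said that clustering will be ignored. The sizing, however, is already fixed on independence, and the only tests named for quantitative outcomes share that assumption.

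**Stable courses of 12 are not in the text.** This stands. The article gives a session capacity and does not say that a woman stays in one course. About 75/18 = 4.2 study-arm women enter per month, so a closed course of 12 would take nearly three months to fill. Fencing is to start within 15 days of enrolment, which points to rolling entry. A full session needs about 12/2.5 = 4.8 masters, and masters vary between sessions. Individually tailored intensity and personalised diets may also lower the correlation.

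**Stronger readings a reader might infer.** One is that the standard error is certainly too small and that the error rate about doubles. The first needs an ICC above zero, which the article neither gives nor rules out. The second is a single point: ICC near 0.05, stable courses of 12 and SDs of 20/10, where the SD of 20 is itself a deliberately conservative choice. Another is that the trial is underpowered. The article plans 75 per group, not 56, and at about 7 courses and ICC 0.05 power remains high. Most of any loss comes from the few degrees of freedom of a course-level test.

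**Conclusion.** The point holds in conditional form. Delivery is grouped in one arm only, while the sizing and the tests named for quantitative outcomes assume independence. Given any positive ICC, the independent-sample standard error is too small. Over ICC 0.01 to 0.10, with the plan's SDs and stable courses of 12, the true error at nominal 0.05 runs from about 6% to about 15%. At ICC 0.05, other course structures move it between about 6% and about 16%. Both the ICC and the course structure are assumptions, so no single figure can be derived from the article. The main issue is the error rate. Power is a lesser one at about 7 courses, but not if there are only 3 or 4 slots.

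**What to change.** **Statistical analysis section.** Analyse DASH and the other quantitative outcomes with a partially nested mixed model: a fixed arm effect, a random course effect in the study arm only (each control a cluster of one), separate residual variances by arm, and Satterthwaite or Kenward-Roger degrees of freedom. Add a sensitivity analysis with clusters defined by master.

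**Data collection section.** Record each woman's course slot and master at every session, so that the cluster can be defined from actual attendance. This has to be done prospectively, because a later analysis plan cannot recover it.

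**Sample size section.** State that 56 per group assumes independence. Give the power at 75 per group over an assumed ICC of 0.01 to 0.10 and the expected number of courses.

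**Cost.** Two fields in the session record, revised analysis wording and a restated power figure. The confidence interval is wider and there are fewer degrees of freedom. At about 7 courses the planned 150 can absorb this. With 3 or 4 slots the power loss is larger and the small-sample correction is itself imperfect, so the expected number of courses should be settled before power is restated.
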